## Abstract

**Introduction:**

Neurological manifestations and complications in coronavirus disease-2019 (COVID-19) patients are frequent. Prior studies suggested a possible association between neurological complications and fatal outcome, as well as the existence of potential modifiable risk factors associated to their occurrence. Therefore, more information is needed regarding the incidence and type of neurological complications, risk factors, and associated outcomes in COVID-19.

**Methods:**

This is a pre-planned secondary analysis of the international multicenter observational study of the COVID-19 Critical Care Consortium (which collected data both retrospectively and prospectively from the beginning of COVID-19 pandemic) with the aim to describe neurological complications in critically ill COVID-19 patients and to assess the associated risk factors, and outcomes. Adult patients with confirmed COVID-19, admitted to Intensive Care Unit (ICU) will be considered for this analysis. Data collected in the COVID-19 Critical Care Consortium study includes patients' pre-admission characteristics, comorbidities, severity status, and type and severity of neurological complications. In-hospital mortality and neurological outcome were collected at discharge from ICU, and at 28-days.

**Ethics and Dissemination:**

The COVID-19 Critical Care Consortium main study and its amendments have been approved by the Regional Ethics Committee of participating sites. No further approval is required for this secondary analysis.

**Trial Registration Number:**

ACTRN12620000421932.

## Introduction

Coronavirus disease 2019 (COVID-19) presents with a wide spectrum of symptoms, from mild to severe, up to sequential organ failure and multiple-organ dysfunction (1). Reports of neurological manifestations associated with COVID-19 are increasing in the literature (2, 3). COVID-19 neurological signs can involve either the central nervous system (CNS), peripheral nervous system (PNS), or musculoskeletal system. Fatigue, myalgia, impaired sense of smell and taste, and headache are common neurological manifestations of COVID-19 (4, 5), whereas dizziness, confusion, delirium, agitation, stroke, hypoxic ischemic injury, seizures, encephalitis and coma among others have been reported neurological complications of hospitalized patients (4, 5). In some cases, neurological manifestations have been reported even without a primary respiratory involvement (4, 5). Several explanations have been proposed for the cause of neurological symptoms of COVID-19, but the underlying pathophysiology is not well defined. Putative mechanisms include viral neurotropism, a hyperinflammatory and hypercoagulable state, or pathological brain–lung crosstalk (6). Endothelial dysregulation (7–9) and pro-thrombotic state (10–12) have been widely suspected to be the possible main contributors of the increased risk of neurologic events. Indeed, COVID-19 patients are at high risk of hypoxia, hypotension, and microvascular abnormalities (13–15) which can promote neuroinflammation and excitotoxicity and increased permeability of the blood brain barrier (16). The risk is even more increased by the use of extracorporeal membrane oxygenation (ECMO) support that is a salvage option in COVID-19 critically ill patients with refractory hypoxemia (17). Prior studies suggested a possible association between neurological complications and mortality (18), but more information is required to delineate this association with respect to regional variation, as well as the risk factors associated to the occurrence of neurological complications (19). The aim of this study is to estimate the incidence of neurological complications in critically ill COVID-19 patients. Associations between neurological complications, patient-level variables and outcomes will also be assessed.

## Methods and Analysis

### Study Design

This is a pre-planned sub-analysis of a large international multicenter observational study of patients in participating intensive care units (ICUs) with COVID-19 of the COVID-19 Critical Care Consortium incorporating the ExtraCorporeal Membrane Oxygenation for 2019 novel Coronavirus Acute Respiratory Disease (ECMOCARD). The collaborative consists of investigators from the Asia-Pacific extracorporeal life support organization (APELSO) in collaboration with centers within the SPRINT-SARI and International Severe Acute Respiratory and emerging Infection Consortium (ISARIC) Network. In Australia, this study is also supported by collaboration with the “National registry on the treatment and outcomes of patients requiring ECMO” (EXCEL Registry). A panel of 13 experts in neurocritical care was created in 2020 together with the main protocol of the COVID-19 Critical Care Consortium by the Steering committee of the consortium. The panel planned this subanalysis and the electronic case report form (eCRF) in February 2020 and followed it up through monthly meeting. The study will be conducted in compliance with the STrengthening the Reporting of OBservational studies in Epidemiology (STROBE) (20) (Supplementary Item 1). Trial registration number: ACTRN12620000421932.

### Objectives

The primary objective is to identify and describe the type and incidence of neurological complications in COVID-19 patients before and after admission to ICU, for all ICU patients selected patient subgroups (sex, age, country, treatment, COVID-19 wave).

Secondary objectives include: To evaluate the effect of neurological complications on outcomes after COVID-19, i.e., mortality, duration of ICU and hospital stay, neurological outcome (modified Rankin scale, mRS) at discharge, incidence of delirium and cognitive outcome at discharge. To identify factors related to the occurrence of neurological complications (including neurological injury due to the antiviral therapy).

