### Inclusion and Exclusion Criteria

The COVID-19 Critical Care Consortium included all COVID-19 patients (≥18 years) admitted to ICU for receiving critical care with confirmed or suspected COVID-19 respiratory disease. For this specific sub-analysis, further inclusion criteria will be available data on neurological complications/manifestations. Patients treated with mechanical ventilation or ECMO for other causes than COVID-19 will be excluded.

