### Statistical Analysis Plan

Planned analyses will comprise of descriptive summaries and regression-based methods for estimating associations between patient-level variables, neurological complications, and outcomes. Descriptive statistics for summarizing the study cohort will be presented as medians with interquartile ranges and frequencies with percentages for continuous and categorical variables, respectively. As an observational study, missing data are expected; a data completeness summary will accompany descriptive summaries for all variables considered. The incidence of neurological complications will be calculated as the number of events per 1,000 ICU days and as the number of events divided by the total number of ICU admissions. Incidence will be estimated per complication using logistic and Poisson regression; Poisson models will include patient days as an offset to account for varying ICU exposure. Baseline models will be adjusted for patient-level variables (e.g., sex, age, country) and calendar time to account for the timing of different COVID-19 waves. Additional covariates will be informed by univariate analysis and penalized regression techniques to address the secondary objective related to incidence.

Analysis of associations between neurological complications and clinical outcomes will be examined using generalized linear mixed models for binary outcomes and parametric survival models for time-to-event outcomes. Evidence of potential associations, including patient demographics and clinical signs assessed during ICU admission, will initially be assessed using univariate analysis. Results of univariate analysis will be used to inform variable selection for multivariable analysis.

Multivariable models for all study objectives will be adjusted for known confounders as fixed or random effects, including study center, country, and calendar time. Model results will be presented as odds ratios (binary outcomes), relative risks (count outcomes) or hazard ratios (time-to-event outcomes) with 95% confidence intervals and *p*-values from hypothesis tests as appropriate.

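### The primary objective asks for a pre-ICU incidence that an ICU-only cohort cannot give, and the models are not limited to complications arising in ICU

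*Protocol article*

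**What the plan says.** Under Objectives, the primary objective covers the "type and incidence of neurological complications in COVID-19 patients before and after admission to ICU", reported "for all ICU patients selected patient subgroups (sex, age, country, treatment, COVID-19 wave" and so on. A secondary objective is "To identify factors related to the occurrence of neurological complications", with no statement about when the complication must have begun.

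Under Inclusion and Exclusion Criteria, patients enter by being "admitted to ICU for receiving critical care with confirmed or suspected COVID-19 respiratory disease". This sub-analysis adds that "further inclusion criteria will be available data on neurological complications/manifestations".

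Under Statistical Analysis Plan, incidence is the "number of events per 1,000 ICU days and as the number of events divided by the total number of ICU admissions". Logistic and Poisson models are fitted for each complication, the Poisson models with patient days as offset for ICU exposure. The same section adds covariates to these models to serve the secondary objective on factors related to incidence. It sets no limit on onset.

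The Introduction gives the target as ICU-level patients: "The aim of this study is to estimate the incidence of neurological complications in critically ill COVID-19 patients". The Discussion and the Conclusions in places speak of incidence in COVID-19 patients, or in COVID-19, without the ICU qualifier.

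**The concern.** An incidence needs a group at risk, followed from a start point. Before ICU admission, that group is COVID-19 patients who might or might not reach ICU. The cohort holds only those who did. Patients with the same complication who stayed on a ward, recovered or died there are absent, and no pre-ICU time is counted.

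Two things are at stake. First, half of the primary objective names a quantity that the design cannot deliver, and a reader of the results could take it as a figure for COVID-19 patients at large. Second, several complications in Table 1 (stroke, status epilepticus, Guillain-Barré syndrome, hypoxic-ischemic brain injury) could themselves help to bring a patient to ICU. If such events count as outcomes in the risk-factor models, the analysis conditions on admission, which both the factor and the outcome may influence. The resulting associations can then partly reflect who gets admitted.

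**Working it through.** The article states no incidence figure, so there is nothing to reproduce. The check sets the sections side by side and then illustrates the size with assumed inputs.

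**1. What can be estimated**

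| Quantity | Numerator | Denominator needed | In the plan? |
|---|---|---|---|
| Incidence after ICU admission | Events with onset in ICU | ICU days or ICU admissions | Yes |
| Incidence before ICU admission | Events before ICU | COVID-19 patients, or their time, at risk before ICU | No |
| Proportion of ICU admissions with an earlier complication | Admissions with an event before ICU | ICU admissions | Yes |

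Only the third row is available for the pre-ICU period.

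**2. How far that proportion can lie from the source-population risk**

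Let p be the risk of a pre-ICU complication in the source population, and R the chance of ICU admission with a complication divided by the chance without. The article gives neither; both are assumed. The proportion among those admitted is q = pR / (pR + 1 − p).

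With p = 0.05:
- R = 0.5: 0.025 / (0.025 + 0.95) = 2.6%
- R = 1: 5.0%
- R = 2: 0.10 / (0.10 + 0.95) = 9.5%
- R = 4: 0.20 / (0.20 + 0.95) = 17.4%

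For p from 1% to 12%, q/p is about 0.5 at R = 0.5 and between 3.4 and 4.8 at R = 5. The figure may be above, below or equal to the source risk.

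**3. What admission can do to an association**

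Among the admitted, odds ratio = true odds ratio × (s11 × s00) / (s10 × s01). Here s is the admission probability; the first index is the risk factor and the second the complication. Baseline admission is assumed to be 10% or 20%.

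- Additive effects, each doubling a 10% baseline: (0.30 × 0.10) / (0.20 × 0.20) = 0.75. Each tripling it: (0.50 × 0.10) / (0.30 × 0.30) = 0.56.
- Logistic effects, each doubling or tripling the odds of admission: 0.75 to 0.93.
- Multiplicative effects, each doubling a 10% baseline: (0.40 × 0.10) / (0.20 × 0.20) = 1.00, no distortion.
- Complication halving admission (its probability, or its odds on the logistic scale) while the factor doubles or triples it: 1.5 to 1.67 (additive), 1.05 to 1.15 (logistic).
- Factor or complication without effect on admission: 1.00.

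**4. Pre-ICU events in the ICU-day rate**

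Assume 1,000 admissions, a mean stay of 15 days (15,000 ICU days) and 60 ICU-onset events. The rate is 60 / 15,000 × 1,000 = 4.0 per 1,000 ICU days. Counting 30 or 60 pre-ICU events as well gives 90 / 15,000 = 6.0 or 120 / 15,000 = 8.0 per 1,000, although none of the added events arose in that time.

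**The case against.** The strongest reply is that the target is ICU patients. The Introduction says so, and the primary objective itself goes on to name all ICU patients. For that target, the share of admissions with an earlier complication is a legitimate descriptive figure, and the plan has its denominator. This stands. A reader might infer that the pre-ICU figure is inflated by selection into ICU. The documents do not support that: against the stated target the figure is misnamed rather than biased, and against a wider population the direction depends on an admission ratio that nobody has stated.

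A reader might also infer that the plan will compare incidence before and after admission, or that it expressly seeks risk factors for pre-ICU events. Neither is written. The objective is descriptive, no contrast is specified, and the risk-factor objective is silent on onset. What remains is that nothing excludes pre-ICU events from the models, although the primary objective that those models serve spans both periods.

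Nor is distorted association a certainty. Under multiplicative admission effects the odds ratio is unchanged. The exclusion of patients ventilated or on ECMO for causes other than COVID-19 also narrows the route by which mainly neurological admissions could enter. The article has no data showing that patients admitted for a neurological event have milder lung disease, so it gives no ground for predicting that severity will look protective.

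Finally, onset rules could sit in an analysis plan or case report form that is not shown. That would cover the detail of the models, but not the primary objective, whose wording is fixed here. The limitations section concedes bias and confounding in general terms and does not name selection by ICU admission.

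**Conclusion.** The point holds in a limited form. As written, the primary objective asks for a pre-ICU incidence that this cohort and these denominators cannot supply. The obtainable quantity is the proportion of ICU admissions with a complication before admission, which describes ICU patients only. This follows from the article's own text and needs no assumption.

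The models, as worded, also let pre-ICU events count as outcomes. The resulting associations can be biased where factor and complication both affect admission. Direction and size cannot be learned from the data. The illustrations (2.6% to 17.4% against an assumed 5%; odds-ratio multipliers from 0.56 to 1.67, including 1.00) rest wholly on assumed admission probabilities and show a possible range, not an expected error.

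The point merits a change because it touches the primary objective and a secondary one, and the remedy is cheap.

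**What to change.** - **Objectives.** Replace the pre-ICU incidence with the proportion of ICU admissions with a neurological complication before admission, and state that it applies to patients admitted to ICU only. Keep the term incidence for complications with onset after ICU admission. Carry the ICU qualifier through the Discussion and Conclusions.
- **Statistical Analysis Plan.** Restrict the incidence and risk-factor models to complications with onset after ICU admission, and enter pre-ICU complications as a baseline covariate.
- **Optional.** Add a sensitivity analysis excluding patients admitted because of the neurological event. This is possible only if the reason for ICU admission is recorded, which the article does not say.

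The cost is rewording and fewer events in the models, which matters most for rare complications. The objective already requires each event to be placed before or after ICU admission. The Discussion lists pre-admission manifestations separately from in-hospital complications. The team should confirm that the case report form dates onset against ICU admission, so that events on the ward before transfer fall on the right side.

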### Specific Sub-analysis

Secondary sub-analyses will also include the investigation of (1) magnetic resonance images (MRI) or computed tomography (CT) features; (2) serum biomarkers [neuronal injury markers (S100B, neuron specific enolase, NSE), endothelial dysfunction markers, inflammatory markers].

### Inclusion and Exclusion Criteria

The COVID-19 Critical Care Consortium included all COVID-19 patients (≥18 years) admitted to ICU for receiving critical care with confirmed or suspected COVID-19 respiratory disease. For this specific sub-analysis, further inclusion criteria will be available data on neurological complications/manifestations. Patients treated with mechanical ventilation or ECMO for other causes than COVID-19 will be excluded.

### Study Procedures and Setting

The protocol of the main study has been previously published (21). Participants in the COVID-19 Critical Care Consortium Observational Study are recruited at multiple sites in over 52 countries from 1st January 2020 onwards.

### Data Collection

Data collection started from the commencement of COVID-19 pandemic and is planned to continue until completion of COVID-19 pandemic, as judged by the World Health Organization. According to the COVID-19 Critical Care Consortium Observational Study protocol (21) and neurological sub-study protocol, the following data will be collected: general patient characteristics, age, gender, body mass index (BMI), country, previous chronic comorbidities, scores of severity; premorbid scores [modified Rankin scale (0–6 points), Figure 1; new neurological complications, laboratory findings, imaging, and management of neurological complications (Supplementary Item 2); patient outcome (mortality at discharge, at 28-days, withdrawal of life-saving therapy and reason; mRS at ICU discharge, mRS at 28 days after discharge). Main eCRF of the COVID-19 critical care consortium study and neuro sub-study are provided in the Supplementary Items 3, 4.

**Figure 1 F1:**
[figure not shown]
Modified Rankin Scale (mRS). The Modified Rankin Score (mRS) is a 6-point disability scale with possible scores ranging from 0 to 6 (from 0 = no symptoms to 6 = dead). A score of 0–3 indicate mild to moderate disability and a score of 4–5 indicate severe disability. From Wade (22).

### Data Management

Data are stored in the central online eCRF database managed by the Oxford University in anonymized form, in order to preserve confidentiality of information in medical records. The Username and password will be assigned by the Oxford University during the registration process for individual Research Coordinators or Site Investigators. All electronic data transfer between study site and database will be username and password protected. The Participant List of the Neurology sub-study is maintained locally and is not to be transferred to any other location. confidentiality of the participant will be maintained unless disclosure is required by law.

Data entry and management will be coordinated by ISARIC and ECMOCARD steering committee, including programming and data management support. ANZIC-RC and ISARIC will act as custodian of the data. The University of Queensland (Australia) will receive data from the data custodians via data sharing agreements. The management committee of the trial will take responsibility for the content and integrity of any data.

### Definition of Neurological Complications

Definition of neurological complications (23–32) is listed in Table 1.

**Table 1 T1:** Definition of neurological complications/manifestations.

**Neurological complication**	**Definition**
**Central nervous system**	
Ischemic stroke (23)	Neurological deficit due to an acute focal injury in the central nervous system caused by vascular involvement such as occlusion and cerebral infarction.
Intracranial hemorrhage (23, 24)	Bleeding that occurs inside the skull. Hemorrhagic stroke: neurological deficit due to an acute focal injury in the central nervous system caused by vascular involvement with intracerebral or subarachnoid hemorrhage. Subdural hematoma: collection of blood under the dura mater.
Encephalitis/meningitis (25)	Severe inflammatory disorder of the brain or meninges or parenchyma.
Transverse myelitis and other spinal cord pathologies (26)	Inflammatory disorder with acute or subacute motor-sensory and autonomic spinal cord dysfunction.
Epilepsy, seizures, and generalized convulsive status epilepticus (27, 28)	Epilepsy is a disorder of the brain characterized by an enduring predisposition to generate epileptic seizures, and by neurobiological, cognitive, psychological, and social consequences. Seizure is a transient occurrence of signs and/or symptoms due to abnormal excessive or synchronous neuronal activity in the brain. Generalized convulsive status epilepticus is defined in adults and children older than 5 years as ≥5 min of (1) continuous seizure or (2) two or more discrete seizures between which there is incomplete recovery of consciousness.
Delirium (29)	Acute change in consciousness and attention caused by an organic condition.

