In the latest 2 years, knowledge has increased regarding extra-pulmonary complications of COVID-19 and their effect on outcome. Severe COVID-19 disease potentially involves multiple organs, including pulmonary, coagulation, cardiac, neurological, renal, hepatic, and gastrointestinal manifestations (34). Many neurological manifestations have been described recently in small observational studies, but additional evidence is needed from large multicentric cohorts. For this reason, in the present study we aim to depict the incidence, risk factors, and impact on outcome of neurological complications in critically ill COVID-19 patients from a large observational multicentric cohort. Data regarding pre-admission neurological manifestations, in-hospital neurological complications as well as ICU-and-hospital length of stay, neurological outcome (mRS), and mortality are available in the eCRF. This sub-analysis of the COVID-19 Critical Care Consortium Observational Study was pre-planned during the first/second wave of the pandemic (late 2020), thus increasing the data quality and minimizing the chance of spurious results and limiting the potential of exploratory learning. The number of patients included in the main study is continuously growing since the beginning of pandemic, allowing to obtain a large sample size, which can provide important information on the current incidence and characteristics of neurological manifestations in COVID-19 patients, evaluating potential associations between predictors and development of neurological complications, and assessing outcomes at discharge from ICU and from hospital and 28-days patients' outcomes. The included patients will be from different countries and centers, including low incoming countries. The patients will be also included during different waves and years of the pandemic, before and after the advent of vaccination campaigns, and with different variants of COVID-19 (i.e., omicron, delta, etc.). This will provide interesting insights on the differences in epidemiology, management strategies, geographical, and economical characteristics of COVID-19 adult patients who manifest neurological complications admitted to ICU. This global research context will provide the lens through which the study as well as its methodological approaches, findings, conclusions, and recommendations can be viewed.

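### Incidence of imaging-dependent complications is compared by country, treatment and wave with no stated step that accounts for who had brain imaging, so differences in detection can be reported as differences in incidence.

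*Protocol article*

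**What the plan says.** All references are to the protocol article.

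- **Objectives.** The primary objective covers the type and incidence of complications overall and in "selected patient subgroups (sex, age, country, treatment, COVID-19 wave".
- **Discussion.** The cohort spans countries of differing resources and several waves, and the authors intend to interpret the contrasts: "This will provide interesting insights on the differences in epidemiology, management strategies, geographical, and economical characteristics of COVID-19 adult patients".
- **Statistical Analysis Plan, denominators.** Events are counted per 1,000 ICU days and per ICU admission, separately for each complication. Both denominators cover the whole cohort.
- **Statistical Analysis Plan, adjustment.** "Baseline models will be adjusted for patient-level variables (e.g., sex, age, country) and calendar time". Further covariates are to come from univariate analysis and penalized regression. Multivariable models also take in study center, as a fixed or random effect.
- **Data Collection.** Imaging is on the list of collected items: "new neurological complications, laboratory findings, imaging, and management of neurological complications". Its only stated analytic use is a secondary sub-analysis of MRI or CT features (Specific Sub-analysis).
- **Table 1.** Ischemic stroke is "Neurological deficit due to an acute focal injury in the central nervous system caused by vascular involvement such as occlusion and cerebral infarction". The intracranial hemorrhage row opens with "Bleeding that occurs inside the skull" and then gives two entities: "Hemorrhagic stroke: neurological deficit due to an acute focal injury in the central nervous system" and "Subdural hematoma: collection of blood under the dura mater".

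**The concern.** Some of the listed complications may be found only when the brain is imaged: ischemic stroke, intracranial hemorrhage, and hypoxic-ischemic injury where imaging makes the diagnosis. If units, treatment groups or periods differ in how readily they scan, the recorded number of such events differs even when the true incidence is the same. Whole-cohort denominators carry that difference straight into the reported rates.

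At stake is the meaning of the subgroup results. A reader shown a higher rate of hemorrhage in one country, in one wave or on ECMO will take it as epidemiology. The plan as described gives that reader no means of judging how much of it is scanning practice.

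**Working it through.** **Text check.** Three questions decide whether the plan already deals with this.

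1. *Does the denominator deal with it?* No. It is all admissions or all ICU days. The extra inclusion criterion for this sub-analysis asks for available data on neurological complications or manifestations; it does not ask for imaging.
2. *Does the named adjustment deal with it?* Not for country. A country term in the model is the contrast being reported, so it contains any country difference in scanning. For treatment and wave, a center effect removes differences between centers that are stable. It does not remove a difference in scanning between treatment groups within a center, or a change in scanning within a center over time.
3. *Does data-driven covariate selection deal with it?* It might bring imaging in, but nothing guarantees that. Imaging would also be a poor covariate, since a scan is often ordered because the event is suspected.

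**Size.** The article states no figure on this point, so there is nothing to reproduce. The illustration below rests on assumed inputs.

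Let *p* be the true incidence (5% in both groups), *s* the share of events found only if the patient is imaged, and *i* the proportion of such patients imaged. Then

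observed incidence = *p* × [(1 − *s*) + *s* × *i*]

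and the apparent ratio is [(1 − *s*) + *s* × *i*₁] / [(1 − *s*) + *s* × *i*₂], which does not depend on *p*.

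Imaging 80% against 30%:

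| *s* | Observed, 80% imaged | Observed, 30% imaged | Ratio |
|---|---|---|---|
| 0 | 5.00% | 5.00% | 1.00 |
| 0.25 | 5% × 0.95 = 4.75% | 5% × 0.825 = 4.13% | 1.15 |
| 0.5 | 5% × 0.90 = 4.50% | 5% × 0.65 = 3.25% | 1.38 |
| 1 | 5% × 0.80 = 4.00% | 5% × 0.30 = 1.50% | 2.67 |

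With a smaller gap, 80% against 60%, the ratio is 0.90/0.80 = 1.13 at *s* = 0.5 and 0.80/0.60 = 1.33 at *s* = 1. With equal imaging in both groups it is 1.00 whatever *s* is.

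**Chance of a false signal.** Take an assumed 2,000 patients per group and imaging of 20% against 60%. At *s* = 0.75 the observed incidences are 2.0% and 3.5%, and a two-sided test at 0.05 would be significant about 83% of the time with no true difference. At *s* = 0.5 they are 3.0% and 4.0%, and the figure is about 41%.

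**The case against.** The best case for the plan is this. The primary objective is descriptive. The limitations section already warns of bias and confounding and disclaims causality. The adjustment list is given by example and is open to additions, center is included, and a data completeness summary is promised. The eCRFs and the supplementary item on complications and imaging are not shown and may define ascertainment. A condensed article may also leave extra tables to the full plan.

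Much of that is fair, and it limits the point. It would be wrong to say that the plan adjusts only for the named variables, or that wave and ECMO contrasts are uninterpretable, since center effects remove part of the problem there. What remains is that the article itself fixes the denominators and the contrasts, and says it will interpret geographical differences. A general caveat about bias does not tell the reader which way, or how far, a given country's figure may be off. A completeness summary shows missing fields; a patient who was never scanned need not have one.

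A reader might also infer from Table 1 that ischemic stroke needs a deficit while any bleed counts, so that in sedated patients the mix of stroke and hemorrhage is distorted. The text does not support this as a general statement. The hemorrhagic stroke entry uses the same deficit wording as ischemic stroke; only the opening sentence of the row and subdural hematoma omit it. Table 1 also sets no bedside examination rule that would exclude sedated patients.

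**Conclusion.** The point holds as a gap in the planned comparison, and it can be repaired. For imaging-dependent complications, following the plan as described can present detection differences as incidence differences. This is most serious for country, where adjustment cannot help, and less so for treatment and wave.

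The size is unknown. The apparent ratios of 1.15 to 2.7 rest on assumed imaging of 80% against 30%, equal true incidence, and a quarter to all of events being found only by imaging. A reader might take 2.7-fold as the expected distortion. That is the extreme case in which no unimaged event is ever recorded, and Table 1 does not make imaging a condition for stroke, so clinically diagnosed cases can still count. If imaging does not differ between groups, there is no distortion from this source.

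A secondary point concerns Table 1. The hemorrhage row is ambiguous: an intracerebral or subarachnoid bleed without a deficit meets the opening sentence but not the hemorrhagic stroke entry, so sites could code it either way.

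**What to change.** In the Statistical Analysis Plan section, for ischemic stroke, intracranial hemorrhage and imaging-diagnosed hypoxic-ischemic injury:

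1. Report the proportion of patients with any brain CT or MRI beside each incidence, by country, wave and ECMO.
2. Add the incidence among imaged patients as a sensitivity analysis.
3. Describe country differences as differences in reported incidence.

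In Table 1, state whether an intracerebral or subarachnoid bleed without a deficit counts as intracranial hemorrhage.

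The cost is one table column, one sensitivity table and two sentences, drawn from data listed as collected. There are two limits. Imaged patients are selected for suspicion, so their incidence will tend to be too high where the whole-cohort figure tends to be too low; the two bracket the value and do not correct it. The analysis also needs the imaging field to be recorded for patients without a complication, which should be checked against the eCRF first.

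I would not redefine ischemic stroke to count infarcts on imaging regardless of deficit. That would make stroke more dependent on who was scanned, and it would change a referenced definition after data collection began.
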